## Abstract

Studies reported that tobacco addiction was related to visual impairments, but one unresolved issue is whether the impairments are related to the many compounds existing in the cigarettes or to the effects of nicotine. On the other hand, nicotine gum can be used as replacement therapy or as a neuroprotective agent for some diseases. The main purpose of this controlled trial is to investigate the effects of nicotine gum on vision. The ENIGMA-Vis trial aims to compare two dosages of nicotine gum (2 and 4 mg) and a placebo gum in a randomized, double-blind, placebo-controlled trial of 100 participants to be allocated into a single group assignment of repeated measures (two studies; *N* = 50 for each one). Eligibility criteria are healthy non-smokers not diagnosed with substance abuse and without an acute or chronic medical condition. Intervention will last three sessions for each participant with a window frame of 1 week per session. Study outcomes are (1) short-term effects of nicotine gum on contrast sensitivity; (2) short-term effects of nicotine gum on chromatic contrast discrimination; and (3) whether demographics, body mass index, or serum cotinine predicts response of visual processing. This study addresses an important gap in the effects of nicotine on vision. One of the main takeaways of this study is to understand the effects of nicotine on contrast sensitivity and chromatic contrast discrimination. This information will provide a further understanding of how nicotine interacts with early visual processes and help determine how the different components present during smoking can affect vision.

**Clinical Trial Registration Number:** RBR-46tjy3.

## Introduction

Smoking is one of the world’s major public health problems. Chronic tobacco consumption, most of the time inhaled by cigarettes, is recognized as a substance use disorder (World Health Organization [WHO], 2015), and nicotine in cigarettes has long been associated with rapid and intense physical dependence (Jasinska et al., 2014). Chronic tobacco smoking is associated with a variety of health problems, including a higher incidence of coronary heart disease, cerebrovascular disease (e.g., stroke and transient ischemic attacks), and vascular diseases (e.g., aortic aneurysm and atherosclerosis) (Fernandes et al., 2018a). Furthermore, oxidative stress caused by chronic smoking is a risk factor for macular degeneration (i.e., a visual loss) (Velilla et al., 2013). Although cigarettes contain other harmful compounds, nicotine is the primary psychoactive compound in them and the most related to tobacco dependence.

A review of studies investigating the effects of smoking on vision provides a reference for examining the effects of nicotine on vision. Studies have shown that more prolonged duration of smoking, in years, resulted in an increased risk of visual loss (e.g., tobacco amblyopia and age-related macular degeneration) as observed using some techniques (e.g., event-related potentials and contrast sensitivity) (Rizzo and Lessell, 1993; Pickworth et al., 1997; Erskine et al., 2004; Fernandes et al., 2018b). The current consensus is that smoking affects vision (Conrin, 1980; Kunchulia et al., 2014; Arda et al., 2015; Fernandes et al., 2018b,c; Silva et al., 2020). However, this topic deserves further investigation as there are questions about the extent of how cigarette affects the (i) lens of the eyes, (ii) pupil, (iii) retina, and (iv) visual pathways. Also, many questions regarding the effects of daily cigarette consumption, duration, and intensity of smoking, age, sex, and the type of cigarette on vision remain to be addressed. More research is required to understand if these impairments are related to the compounds of cigarettes or nicotine intake. The roles of both tobacco smoking and nicotine addiction (due to smoking use) and the interactions with the nicotinic acetylcholine receptors (nAChRs) remain a matter of ongoing discussion.

Nicotine binds to the nAChRs and changes the receptor’s conformation, opening the ion channels and allowing sodium and calcium to enter causing depolarization and facilitating the release of a variety of neurotransmitters throughout the brain via α7 and β2 subunits (Dani, 2015). Low concentrations of nicotine (equivalent to smoking one or two cigarettes; Russell et al., 1976) facilitate the release of glutamate, gamma-aminobutyric acid (GABA), and dopamine neurotransmitters. The release of these neurotransmitters, in low concentrations, regulates synaptic plasticity in several areas of the central nervous system and has been implicated with improvement in some cognitive functions like memory and attention (Ellis et al., 2006; Hasselmo, 2006). Nicotine exposure seems to produce short-term effects on the release of some neurotransmitters and improve brain functions. These positive short-term effects have led to using nicotine as a neuroprotective agent for some diseases (e.g., Parkinson’s disease) (Quik et al., 2012); on the other hand, chronic tolerance (e.g., via chronic smoking) leads to the development of a long-lasting negative feedback loop on the release of neurotransmitters, decreasing the number of nAChRs due to desensitization (Halappanavar et al., 2013).

Nicotinic receptors are found throughout the visual system including the retina, lateral geniculate nucleus (LGN; both ventral and dorsal regions), the suprachiasmatic nucleus, primary visual cortex, fusiform gyrus, and prefrontal cortex (Paterson and Nordberg, 2000; Levin, 2001; Metherate, 2004; Govind et al., 2009). The role of the nAChRs within the retinal circuitry is still being worked out. However, the homomeric and heteromeric nAChRs (mostly α2–α7 and β2 subunits) have been found on the cones and rods photoreceptors (e.g., cell body, synaptic body, and synaptic terminals). nAChRs are also expressed in horizontal cells (e.g., dendrites and axons), bipolar cells (e.g., dendrites), amacrine cells (e.g., dendrites), and the ganglion cells (e.g., dendrites, cell bodies, and axons). Most of the nAChRs subtypes (from α2 to α8 and from β2 to β4) are found in these cells, but there is a greater heterogeneity in their expression. In the intrinsically photoreceptive retinal ganglion cells (ipRGCs), the α/β combination is expressed on their dendrites; however, the role of the nAChRs in the ipRGCs is still unclear (Paterson and Nordberg, 2000; Neal et al., 2001; Iwamoto et al., 2013; Dani, 2015).

The retinal circuitry carries out early processing of luminous contrast (achromatic) and chromatic information. The information from the retina is relayed to the LGN via three different pathways on the basis of where they project into the LGN. The parvocellular pathway is believed to carry both luminous contrast information for fine detail along with chromatic information based on the long- (L) and middle- (M) wavelength sensitive cones. The magnocellular pathway relays luminous contrast information for low-contrast, coarse (or large) detail in their cells (Govind et al., 2009; Fernandes et al., 2018c). The koniocellular pathway carries chromatic information on the basis of the short (S) wavelength sensitive cone and both the M- and L-cone responses. The pathways are maintained from the LGN to the visual cortex, where the color and luminous contrast information is combined to provide the visual perception (Cornsweet, 2012). The majority of the nAChRs in the LGN are expressed in the parvocellular pathway, but nicotine also has an affinity for the magnocellular and koniocellular pathways (Govind et al., 2009). Acetylcholine and nicotinic inputs modulate some features of stimulus like orientation and direction (Sillito and Kemp, 1983; Roberts et al., 2005; Zinke et al., 2006).

Because nAChRs are present throughout the visual pathway, both basic chromatic and luminous contrast perception could be affected. Nevertheless, it is unclear as to whether the extent of these processes would be differently affected. The result that the majority of nAChRs are located within the parvocellular pathway suggests that color information along the red–green (L-cone—M-cone) dimension could be affected more than along the blue–yellow dimension (S-cone pathway), and contrast sensitivity for high spatial frequencies could be affected more than contrast sensitivity at low spatial frequencies. This hypothesis assumes that the net result of nicotine at the retinal level does not differentially affect the inputs into the three LGN pathways. However, it is unclear whether greater heterogeneity in the expression of retinal nAChRs subunits would play a role in these inputs. Our study attempts to investigate, without establishing a causal relationship, whether the achromatic and chromatic contrast discrimination will be differentially affected, for example.

The primary use of nicotine is for nicotine replacement therapy in order to reduce withdrawal symptoms that occur during smoking cessation. Methods of administration include gum, lozenges, transdermal patches, nasal spray, and inhaler. The gum yields blood nicotine levels, similar to those after smoking cigarettes (Russell et al., 1976). The choice of using nicotine gum instead of other methods of nicotine administration was related to its low cost, fast absorption (compared to transdermal patches), high bioavailability, easy consumption, availability in low doses (2-mg and 4-mg), and fewer side effects (Fagerström et al., 1993; Aslani and Rafiei, 2012).

The effects of nicotine gum on vision are currently unclear. To this date, only two studies investigated the effects of nicotine gum on the visual system. Varghese et al. (2011) investigated the effects of nicotine gum in 10 healthy non-smokers. Their main results indicated that a 2-mg dose decreased amplitude in dark-adapted b-wave but had no effect in light-adapted b-wave. Similarly, a 4-mg dose decreased dark-adapted b-wave but increased light-adapted b-wave amplitudes. The b-wave reflects changes in primarily the bipolar cells activity and also the Müller glial cells, amacrine cells, and ganglion cells (see Silverstein et al., 2020, for a review). The increase in the amplitude could be due to nicotine increasing the release of dopamine in the retina. Increasing retinal dopamine does (or could) increase the amplitudes of the b-wave ([name], e-communication), which could explain why the cone-mediated photopic b-wave increased; however, it would not explain the reduction in the rod-mediated scotopic b-wave unless dopamine was an inhibitory neurotransmitter within the rod pathways. Nevertheless, the perceptual consequences of these changes are uncertain.

The other study was investigating how nicotine affected color perception. Naser et al. (2011) observed that the use of nicotine gum reduced the total error score (TES) of the Farnsworth–Munsell Hue (i.e., improved chromatic discrimination) and decreased the threshold for detection of a red spot on white background in two healthy non-smokers. The improvement in the TES was larger for the 4-mg dosage compared with the 2-mg dose. On the other hand, the change in the red light detection threshold was larger for a 2-mg dose than a 4-mg dose.

One needs to be careful when interpreting the outcomes of these two experiments because the nicotine may not have been at the peak concentration within the system. Varghese et al. (2011) tested individuals after 30 min of nicotine exposure. As reported by Russell et al. (1976), the peak occurs between 15 and 40 min, after the beginning of the chewing. Thus, conducting an experiment after 30 min of nicotine gum administration could be outside the peak concentration. Naser et al. (2011) did not report the time window. Other limitations include their sample sizes were small, and neither experiment used a blind, controlled design.

The two studies on nicotine and vision suggest that nicotine could enhance photopic vision; however, studies on smoking suggest that nicotine, or another component in tobacco smoke, could impair photopic visual processes slightly by decreasing the pupil size and thereby reducing retinal illumination (Kunchulia et al., 2014; Erdem et al., 2015).

The Effects of Nicotine Gum on Vision Administration (ENIGMA-Vis) is, to the best of our knowledge, the first randomized controlled clinical trial that aims to develop a framework to investigate the effects of nicotine gum on basic visual processing. Here, we discuss the rationale, methods, and design of our ongoing trial. The main aim is to test if individuals have improvements in early-stage visual processing from nicotine gum administration (Levin, 2001). The primary hypothesis guiding our trial is that individuals using higher doses of nicotine gum will show better visual processing. The secondary hypotheses are that (a) differences in visual performance are mediated by the body mass index (BMI), sex (e.g., metabolism for nicotine is different between males and females) but not for other demographic data (e.g., age); and (b) differences in visual performance are mediated by the serum cotinine concentration.

This protocol is divided into two studies: the first study investigates contrast sensitivity, using the Metropsis software in healthy non-smokers. The gratings will be oriented vertically at spatial frequencies ranging from 0.2 to 20 cycles per degree so that the resolution capabilities of both the parvocellular and magnocellular pathways are assessed. The second study investigates chromatic contrast discrimination in healthy non-smokers using the Cambridge Colour Test (CCT). This test will measure discrimination along the individual cone dimensions and overall color discrimination relative to three different reference backgrounds. The measurements along the cone dimensions would help determine whether the three chromatic signals are differentially affected, and the overall discrimination would be a replication and/or an extension of the Naser et al. (2011) experiment. Findings obtained from this study will help to provide motivation for follow-up studies (e.g., comparing acute with chronic use of nicotine). The findings may help refine public health policies regarding tobacco use disorder, given the significance for public health. For example, if healthy non-smoking individuals can benefit from acute nicotine use, other studies may investigate whether smokers will receive the same benefit for their vision when they are using nicotine gum to quit smoking. We believe our study can contribute to the development of the field. Having reviewed related work, we now present the main body of our research.

## Methods and Analysis

### Aims

#### Study 1—Contrast Sensitivity Function

The first study will not be conducted simultaneously with the second study because it is a within-subject, and we cannot exclude the possibility of desensitization among individuals; therefore the participants enrolled in this first study will not participate in the second study. The primary aims for the contrast sensitivity function (CSF) measurements are investigating whether any of three conditions (placebo, 2-mg, or 4-mg doses) (a) influence visual performance for low, middle, and high spatial frequencies (ranging from 0.2 to 20 cycles per degree); (b) whether there is a dose dependency on contrast sensitivity; (c) whether BMI (we intend to select a pool of individuals with different BMIs) influence the results; (d) if there are differences related to sex; and (e) whether there is a serum cotinine concentration dependency of contrast sensitivity. Exploratory aims will test effects by age, height, weight, and years of education.

#### Study 2—Cambridge Colour Test

The primary aims of this second study period are investigating whether any of three conditions (placebo, 2-mg, or 4-mg doses) (a) influence chromatic contrast discrimination for the S-, M-, and L-wavelength sensitive cones (blue, green, and red, respectively) using the Trivector subtest; (b) influence the position and direction (e.g., larger or more circular ellipses indicate worse discrimination) of an MacAdam chromatic discrimination ellipse for on an achromatic background (Ellipse 1); (c) determine whether there is a dose effect; (d) determine whether there is an interaction between the dosages and direction of the chromatic contrast discrimination; (e) are the results related to BMIs; (f) are different with regard to sex; and (g) determine whether there is an interaction between cotinine concentration and chromatic contrast discrimination. Exploratory aims will test effects by age, height, weight, and years of education.

### General Study Design

The ENIGMA-Vis is designed to be a randomized, double-blind, and placebo-controlled three-period trial (RBR-46tjy3) to investigate the effects of nicotine gum administration on vision. The diagram is shown in Table 1. This trial comprises three main gum administrations (placebo, 2-mg, and 4-mg doses). Participants will be followed up at 4 weeks, and the assessments will be performed in week 0 (baseline) to week 3. Female participants will be tested outside their luteal phase.

**TABLE 1 T1:** Measures by timepoint for the schedule of enrolment, interventions, and assessments.

	**Study period**					
	**Enrolment**	**Allocation**	**Post-allocation**			**Close-out**
**Timepoint**	**−*t*_1_**	**Week 0**	**Week 1**	**Week 2**	**Week 3**	**40 weeks**
**ENROLMENT**						
Eligibility screening	X					
Informed consent	X					
Neuropsychological measures		X				
Allocation		X				
**INTERVENTIONS**						
Nicotine gum 2 mg						
Nicotine gum 4 mg						
Placebo gum						
**ASSESSMENTS**						
(Sex, age, level of education, height, weight, body mass index, serum cotinine)		X				
Contrast sensitivity measures (*n* = 50)			X	X	X	X
Color vision measures (*n* = 50)			X	X	X	X
Secondary outcomes			X	X	X	X

### Participants

Healthy non-smokers from 18 to 40 years are eligible for the study. We intend to recruit participants over the phone, radio, websites, and newspaper advertisements. An initial screening for eligibility will be done over the phone, 30 days before the start of the study. Potential participants will be invited to schedule a baseline enrollment (Figure 1). After signing an informed consent, the participants will be assessed for eligibility. Inclusion and exclusion criteria are presented below.

**FIGURE 1 F1:**
[figure not shown]
Flowchart of the ENIGMA-Vis. **(A)** represents the screening of the participants and the general design of this trial. **(B)** represents the flowchart of Study 1 or Study 2.

### Eligibility Criteria

An investigator, on the basis of the criteria reported below, will determine eligible participants.

#### Inclusion Criteria

All of the participants must sign written informed consent before entry into the study, fulfill the criteria for never smokers (smoked < 15 cigarettes per lifetime; Pomerleau et al., 2004), and be willing and able to comply with the scheduled visits and other trial procedures. The participants should have normal dental status and chewing ability. Finally, the participants would be required to be diagnosed free of ocular diseases by an ophthalmologist during the previous 12 months. All of the participants should have normal or corrected-to-normal vision as determined by visual acuity of at least 20/20 (logMAR ≤ 0.0, using the FrACT; Bach, 1996). All of the participants will be screened for color blindness using the 24-plate edition of the Ishihara test (Ishihara, 1972). More than three errors will be considered a failure (Fernandes et al., 2020). All of the participants will be asked to abstain from caffeine-containing products beginning at midnight the evening prior to the measurements (Fernandes et al., 2018a). The participants will be assessed for caffeine dependence or withdrawal using self-reports. The participants will be assessed for second-hand smoke. The Smoke Scale for Adults (SS-A; Misailidi et al., 2014) will be used as this is a valid, reliable, and practical scale for adults.

#### Exclusion Criteria

Exclusion criteria will be <18 or >40 years old, current history of neurological disorder, cardiovascular disease, pregnant or suspected of being pregnant, a history of head trauma, and a history of contact with such substances as solvents, caffeine addiction or deprivation, and current use of medications that may affect visual processing and/or cognition (e.g., benzodiazepines or antidepressants). Importantly, other acute or chronic conditions will be defined using the *Structured Clinical Interview for Diagnostic and Statistical Manual of Mental Disorders*, 5th edition (American Psychiatric Association, 2013) that may bias the results of this trial will be considered as an exclusion criterion. Individuals with a score of >16 in the SS-A will be excluded. Individuals who participated in other clinical trials in the previous months will be excluded. Finally, neuropsychological testing will be conducted to identify the possibility of cognitive impairment. The tests will include the Mini-Mental State Examination (Folstein et al., 1975) and the Trail Making Tests (Tombaugh, 2004). Individuals with scores ≤ 24 on a paper-based Mini-Mental State Exam (Folstein et al., 1975) and scores below the normative data for age and education in the Trail Making Tests (cutoffs based on the normative data for age and education) will be excluded (Tombaugh, 2004).

### Baseline Measures

All of the baseline measures will be assessed in the allocation phase (see Table 1) at the laboratory. The baseline measures of the participants will include age, sex, height, weight, BMI ($\text{BMI}=\,\frac{\text{Weight}}{{\text{Height}}^{2}}$), and serum cotinine levels. Also, for female participants, information about the menstrual cycle and pregnancy will be assessed. Serum cotinine samples will be collected as a screening to avoid previous nicotine use (biological markers) using 10 ng/ml as a cutoff (Duque et al., 2017). The serum sample will be taken randomly selecting (or selected in order to ensure a balanced representation of gender and BMI) ≥ 50 participants and stored at or below −20°C. They will be measured using a microplate enzyme immunoassay kit, according to the manufacturer’s instruction. Serum cotinine will also be used as secondary outcomes (see “Outcome Measures” section).

### Randomization/Stratification and Blinding/Masking

We will use lists to classify, identify, and separate participants according to randomization, allocation, blinding of outcomes, initials of the participants, and adverse effects.

#### Randomization

Participants will be randomized in accordance with a 1:1:1 permuted block randomization generated by a free resource for researchers^1^. Allocation will be made according to the Cochrane guidelines (Higgins et al., 2019). The main purpose of using a computerized randomization program is to minimize confounding factors and avoid differences between the participants in Study 1 and Study 2 (e.g., similar, or approximately, number of males and females). Fifty participants will be allocated to Study 1, and 50 participants will be allocated to Study 2. All participants will be designated with their initials and a random number by a researcher who is unaware of the condition assignment.

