### Outcome Measures

The primary outcomes of this study are about the effects of nicotine on achromatic contrast sensitivity at the various spatial frequencies (Study 1) and on chromatic contrast discrimination using the Trivector threshold values and the various elliptical parameters like angle of the major axis, major axis length, axis ratio, and area (Study 2). For Study 1, the higher the curve, the better the discrimination ability. For Study 2, the area of the ellipse is a general index of chromatic discrimination. That is, the smaller the ellipse, the better the discrimination ability. Provided that there is a statistically significant main effect or interaction, results will be related to the statistical analysis: an improvement of 10% will be considered as meaningful difference for each spatial frequency (Study 1) and for each parameter of the CCT (Study 2). The primary outcome will be assessed after the three sessions are completed. As previously noted, we did not observe learning or practical effects when using Metropsis software (Fernandes et al., 2019a) and the CCT (Fernandes et al., 2020). The secondary outcomes are related to demographic data (effects of age, years of education, height, and weight), BMI, and gender effects. Serum cotinine levels (ng/ml) after each session (placebo, 2 mg, and 4 mg of nicotine gum) will be used as predictors of response (for each visual test) in a multivariate regression analysis. Data will be double-checked and stored at an open access repository (figShare; available upon request).

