#### Study 2—Cambridge Colour Test

For the Trivector subtest of the CCT, we will use a one-way MANOVA, with three dependent variables (thresholds for protan, deutan, and tritan; continuous variables), and one independent, within-subject variable (condition ∼ three levels). For the Ellipse subtest, we will conduct a separate MANOVA for Ellipse 1 with two dependent variables (angle and area; continuous variables) and one independent, within-subject variable (condition ∼ three dosage). A moderation or mediation analysis (using 5,000 bootstrapping resamples) will be conducted to determine whether the area, length, angle, or ratio is a better predictor of any results of the CCT.

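### All participants receive all three gums, but the plan does not say that gum order is what the 1:1:1 list randomises, and the primary models do not adjust for period

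*Protocol article*

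**What the plan says.** **Design.** The Abstract has participants "allocated into a single group assignment of repeated measures", with three sessions each. General Study Design calls it a "randomized, double-blind, and placebo-controlled three-period trial". Condition (placebo, 2 mg, 4 mg) is a within-subject factor in both studies.

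**Randomisation.** The Randomization section states: "Participants will be randomized in accordance with a 1:1:1 permuted block randomization generated by a free resource for researchers". It does not say what the three equal parts are. The computerised list is meant to "minimize confounding factors and avoid differences between the participants in Study 1 and Study 2". Blinding/Masking adds only that the coordinator produces the allocation list.

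**Analysis.** The Study 1 model is a MANOVA of eight spatial-frequency thresholds, with condition as the one independent variable. For the Trivector subtest in Study 2, "we will use a one-way MANOVA, with three dependent variables" and again condition alone; the Ellipse MANOVA has the same structure. Additional Analyses adds no period, sequence or carry-over term.

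**Persistence and session effects.** The caption of Figure 2 gives a one-week washout. Safety, Dropouts, and Adherence allows flexible visits up to a maximum of one week apart and sets no minimum there. The Study 1 aims keep participants out of Study 2 because "we cannot exclude the possibility of desensitization among individuals". For both tests, Outcome Measures cites earlier work in which "we did not observe learning or practical effects".

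**The concern.** In a three-period crossover, randomising the order of treatments keeps session effects (practice, fatigue, expectation, growing guesses about the gum) apart from dose effects. The plan's randomisation text is not tied to that task. A 1:1:1 ratio fits neither parallel gum arms, since there are none, nor a split of 100 people into two studies of 50. Part of its declared purpose protects a between-study comparison that the analysis sections do not make.

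The models then leave period out, so any session effect goes into the error term or, if the orders are unequal, partly into the dose contrast. Carry-over is a separate matter. The document doubts that desensitisation clears between studies, and the same doubt applies to three sessions a week apart in the same person. At stake are the precision of the dose contrasts and, depending on which orders are used, how well they are protected from residual effects.

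**Working it through.** The plan gives no figure for drift, carry-over or order counts, so there is nothing of its own to reproduce. The sizes below are assumptions; the design facts are from the protocol.

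**1. What can 1:1:1 refer to?** Three parallel arms: excluded, because everyone receives all three gums. Two studies: excluded, because 50 and 50 is 1:1. Three gum orders: possible, but not stated. Fifty people would split 17/17/16 over three orders, or 9/9/8/8/8/8 over six.

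**2. Period omitted, orders balanced.** Let vision drift by delta residual SDs per session. For 4 mg minus placebo, the gap in session number is:
- three cyclic orders (P-2-4, 2-4-P, 4-P-2): +2, -1, -1; mean 0, mean square (4+1+1)/3 = 2
- six orders: +2, +1, +1, -1, -1, -2; mean 0, mean square 12/6 = 2

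The drift therefore adds 2 x delta^2 x sigma^2 to a paired-difference variance of 2 x sigma^2, a factor of 1 + delta^2:
- delta = 0.2: 1.04, or +4%
- delta = 0.5: 1.25, or +25%

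The mean gap is 0, so there is no bias.

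**3. Type I error with period omitted.** Null simulation: n = 50, alpha 0.01, total SD 1, within-person correlation 0.5 (assumed), 4,000 runs per setting, univariate repeated-measures F test, drift 0 to 0.5 total SD per session. With order randomised or balanced, the rejection rate is at most about 0.015 and the bias at most about 0.03 SD. At a drift of 0.5 SD the condition-only test becomes conservative: 0.0015 with three cyclic orders and below 0.001 with six, against about 0.01 and 0.008 when period is fitted. The cost is power.

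**4. Carry-over adjusted for.** Least squares with participant, period and direct effects, with and without first-order carry-over. Variance of 4 mg minus placebo, in units of sigma^2/N:

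| Orders | Without carry-over | With carry-over |
|---|---|---|
| Three cyclic | 2.0 | 10.0 |
| All six | 2.0 | 2.5 |

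The ratio 10.0/2.5 = 4 arises because, in a cyclic square, each gum is only ever preceded by one other gum.

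**5. Carry-over present but not adjusted for.** Assume 4 mg leaves a residue of 0.2 SD in the next session. In the cycle P-2-4, placebo follows 4 mg in two of three orders, so 4 mg minus placebo shifts by -0.2 x 2/3 = -0.13 SD. With six orders it follows in two of six: -0.2 x 2/6 = -0.07 SD (about -0.06 in the simulation). Fitting period does not remove this.

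**6. Unequal dropout, period omitted.** Three cyclic orders, 40 completers, assumed drift of 5% per session.
- P-2-4 depleted to 10, the others 15: (10 x 2 - 15 - 15)/40 = -0.25 sessions; x 5 = -1.25 percentage points.
- Either other order depleted: (15 x 2 - 10 - 15)/40 = +0.125 sessions; x 5 = +0.625 points.

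**The case against.** The best defence is that nothing in the document says order is fixed or unbalanced. The trial is called randomised, three-period and repeated-measures. Since 1:1:1 fits no other unit, three gum orders is the natural reading. A journal article may leave the list of orders to the full protocol, and Figures 1 and 2, which illustrate the flow and the procedure, were not available here. This stands as far as it goes: balance is not shown, which is different from shown to be absent.

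A reader might infer that everyone takes the gums in one order. The simulation above would then give a bias of 0.20 SD and a type I error of 0.087 at a drift of 0.1 SD per session, and 0.40 SD and 0.46 at 0.2 SD. The documents do not support that reading.

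A reader might also infer that desensitisation across sessions is ignored. It is not: a one-week washout is stated, and a washout is the usual design answer to carry-over. Two passages weaken it. The Study 1 aims doubt that desensitisation can be excluded, and the visit rule sets a ceiling on the interval with no floor.

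The no-learning statement is a stated reason to expect little practice drift, and it counts against the larger drifts assumed above. It does not address desensitisation, expectation or unblinding over sessions.

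Finally, period terms are often left to the analysis plan. Here, however, the article specifies the primary models and names condition as the only independent variable, so the omission is stated rather than merely undetailed.

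**Conclusion.** The point holds as a gap in what is fixed and as a model that can be improved cheaply. The unit allocated 1:1:1 is not stated, part of the stated purpose concerns a comparison that no listed analysis makes, and the primary models omit period.

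The size depends on facts the document does not give:
- If order is balanced, the loss is mainly precision (4% to 25% more variance for assumed drifts of 0.2 to 0.5 residual SD per session), without material inflation of type I error.
- The fourfold variance ratio applies only if 1:1:1 means three cyclic orders and first-order carry-over is fitted. Without carry-over the two designs are equal.
- The dropout bias is 0.6 to 1.25 points under an assumed 5% drift, depending on which order is depleted. The upper figure is the worst case, and it is small against the 10% difference the plan calls meaningful.

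This should be changed, but it does not by itself invalidate the trial.

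**What to change.** 1. State that gum order is randomised within each study, to all six sequences in permuted blocks. Stratifying by sex is optional.
2. Add period as a fixed effect, with participant as a random effect, to the primary models. In practice this means a mixed model across the thresholds in place of the condition-only MANOVA; it also fits the maximum likelihood approach already named for missing data.
3. Report a first-order carry-over term as a sensitivity analysis only.
4. Correct the stated purpose of the randomisation so that it refers to balancing gum order over sessions, not to similarity of Study 1 and Study 2.
5. Reconcile the visit-interval rule under Safety, Dropouts, and Adherence with the washout in the caption of Figure 2.

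The cost is a new randomisation list before enrolment and two degrees of freedom for period, with no added visits or participants. The Ethics Statement says that nobody had yet been recruited.
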